## Abstract

**Background:**

It had been reported that up to 37% of the adult male population smokes cigarettes in Qatar. The Global Youth Tobacco Survey also stated that 13.4% of male school students aged 13 to 15 years in Qatar smoke cigarettes. Smoking cessation is key to reducing smoking-related diseases and deaths. Healthcare providers are in an ideal position to encourage smoking cessation. Pharmacists are the most accessible healthcare providers and are uniquely situated to initiate behavior change among patients. Many studies have shown that pharmacists can be successful in helping patients quit smoking. Studies demonstrating the effectiveness of pharmacist-delivered smoking cessation programs are lacking in Qatar. This proposal aims to test the effect of a structured smoking cessation program delivered by trained ambulatory pharmacists in Qatar.

**Methods/Design:**

A prospective, randomized, controlled trial is conducted at eight ambulatory pharmacies in Qatar. Participants are randomly assigned to receive an at least four-session face-to-face structured patient-specific smoking cessation program conducted by the pharmacist or 5 to 10 min of unstructured brief smoking cessation advice (emulating current practice) given by the pharmacist. Both groups are offered nicotine replacement therapy if feasible. The primary outcome of smoking cessation will be confirmed by an exhaled carbon monoxide test at 12 months. Secondary outcomes constitute quality-of-life adjustment as well as cost analysis of program resources consumed, including per case and patient outcome.

**Discussion:**

If proven to be effective, this smoking cessation program will be considered as a model that Qatar and the region can apply to decrease the smoking burden.

**Trial registration:**

Clinical Trials NCT02123329.

## Background

The leading preventable cause of ill health today is cigarette smoking [1]. It is a major risk factor for several causes of death including heart disease, chronic lung diseases and lung cancer [2]. It kills one in ten adults globally and causes more than 5 million deaths annually. If present trends continue, the number of smoking-related deaths is expected to reach more than 8 million deaths per year by 2030 [3]. The adverse health consequences of tobacco use not only compromise smokers’ quality of life, but also entail significant direct and indirect economic costs on society. The 2008 World Health Organization (WHO) report states that the global healthcare costs attributable to tobacco use reach hundreds of billions of US dollars each year [4]. Smoking cessation is key to reducing the number of smoking-related diseases and deaths. At any age, quitting smoking improves quality of life (QoL) and confers considerable health benefits including reduced risk of coronary heart disease, stroke and smoking-related cancers [5,6]. The World Bank suggests that if adult tobacco consumption were to decrease by 50% by the year 2020, approximately 180 million tobacco-related deaths could be avoided between now and 2050 [7]. Health professionals are in an ideal position to encourage smoking cessation. A short intervention by them can considerably increase the smoking cessation rate [8]. Of all health professionals, pharmacists are the most easily accessed by the public and are uniquely situated to initiate behavior change among smokers [9]. They can provide education and advice without prior appointment and with no direct or additional cost to individuals [10]. They regularly interact with patients obtaining medications for smoking-related diseases. In addition, the increased availability of pharmacologic smoking cessation aids including some formulations of nicotine replacement therapy over the counter in pharmacies in many countries gives the pharmacists a distinct opportunity to serve as front-line health providers who can play a major smoking cessation role [11]. Moreover, available data support the provision of smoking cessation services in ambulatory and community pharmacies. Many studies have shown that pharmacists can be effective providers of tobacco cessation interventions and can be successful in helping patients quit smoking [12-20] and that these pharmacy interventions can be cost-effective or cost-beneficial [21-24]. Additionally, in many countries there is extensive support at the professional level for the involvement of pharmacists in smoking cessation. The Canadian Pharmacists Association developed a Joint Statement on Smoking Cessation. This statement promotes the involvement of health professionals including pharmacists in tobacco prevention and cessation [8]. The International Pharmaceutical Federation (FIP) issued a statement of policy on the role of pharmacists in promoting a tobacco-free future [25]. The European Forum adopted a pharmacists’ charter on action against smoking, which states that pharmacists should consider smoking cessation as an essential element of their professional responsibilities [26]. The US Public Health Service published evidence-based clinical guidelines recommending that all health care providers, including pharmacists, should offer smoking-cessation interventions [27]. The American Society of Health-System Pharmacists’ (ASHP) Therapeutic Position Statement on the Cessation of Tobacco Use strongly encourages pharmacists as well as other healthcare providers to integrate identification of tobacco users and delivery of tobacco-cessation interventions into their routine patient care. As per the ASHP statement, these interventions should address five key elements of comprehensive tobacco cessation counseling (the 5 As): (1) asking patients about tobacco use, (2) advising users to quit, (3) assessing their readiness to quit, (4) assisting them with quitting using behavior modification and smoking cessation medications, and (5) arranging follow-up care. If comprehensive tobacco-cessation counseling cannot be provided because of time constraints or practice site logistics, pharmacists can use a truncated 5 A model whereby they ask about tobacco use, advise tobacco users to quit, and then refer patients to smoking cessation providers or programs [28].

In Qatar, tobacco use is a major public health problem that, in addition to the associated morbidity and mortality, constitutes a huge burden on healthcare services. To control tobacco use, Qatar has adopted the international approaches recommended by the World Health Organization (WHO) and regional plan of Arab countries in the Gulf. These approaches are based on three strategies: (1) imposing legislative tobacco control measures, for example, banning smoking in enclosed public places and prohibiting selling cigarettes, tobacco or its derivatives to anyone less than 18 years old, (2) providing smoking cessation services for free in two hospital-based smoking cessation clinics and (3) implementing antismoking public awareness activities [29]. Despite these approaches, in Qatar up to 37% of adult males currently smoke tobacco [30] and 13.4% of male school students aged 13 to 15 years smoke cigarettes according to the 2007 Global Youth Tobacco Survey [31]. Furthermore, smoking-related diseases are the most prevalent in Qatar. Ischemic heart disease, as an example, was ranked as one of the leading causes of burden of disease in Qatar in 2010 [32], and Qatar has a higher age standardized lung cancer incidence rate than many countries in the Gulf (8.95 per 100,000) [33]. In addition, according to a recent survey done by Weill Cornell Medical College in Qatar, at least 1 billion cigarettes are smoked in Qatar each year, averaging 12,000 per individual, and 65 million US dollars (USD) are spent on cigarettes annually; 150 million USD are used to cover the healthcare costs of patients affected by smoking-related diseases [34]. The potential for pharmacist-assisted tobacco cessation is therefore huge and could have a considerable impact on smoking rates, prevention of tobacco-related diseases and enhancement of public health in Qatar. Around 700 registered pharmacists practice in public and private ambulatory care clinics and in community pharmacies in Qatar. If each of these pharmacists successfully assists just one tobacco user in quitting each month, this would result in more than 8500 quitters annually. However, according to a study conducted by Qatar University’s College of Pharmacy and funded by the Qatar Foundation under its Undergraduate Research Experience Program (UREP), Qatar’s ambulatory and community pharmacists are not fully engaged in smoking cessation activities. Eighty percent of Qatar’s ambulatory and community pharmacists rarely, never or sometimes ask their patients about their smoking status, and 53% rarely, never or sometimes offer smoking cessation counseling to nicotine therapy purchasers. When meeting patients who smoke, only 45% of pharmacists discuss the adverse health effects of smoking, 41% assist them in quitting and 16% arrange follow-up sessions with them to assess their progress in quitting smoking. However, more than 85% of pharmacists are interested in providing smoking cessation counseling and believe that it is an important activity [35]. The pharmacists’ perceptions regarding the importance of smoking cessation can be transformed into action if a smoking cessation model is provided that these pharmacists can use in routine practice. Unfortunately, an intensive, patient-specific program of smoking cessation designed exclusively for implementation in community and ambulatory pharmacies is not available in Qatar. In addition, evidence regarding the effect of such a program is lacking in Qatar.

Also important, in addition to the numerous knowledge gaps identified above in relation to Qatar, there are also no data on how cost beneficial the running of smoking cessation programs like the currently proposed one is, added to a lacking data on the associated resource implications in the pharmacy setting from the Qatari perspective.

### Study objectives

This proposal describes a study that is currently being implemented in eight public and private ambulatory clinic pharmacies in Qatar. Our hypothesis is that a patient-specific structured smoking cessation program delivered by smoking cessation-trained ambulatory pharmacists would be significantly more effective in helping smokers stop smoking and achieving long-term smoking abstinence than brief unstructured pharmacist-delivered advice.

We also hypothesize that quitting smoking would lead to significant improvement in health-related quality of life.

The study objectives are:Primary: To test the effect of a face-to-face structured patient-specific smoking cessation program delivered by trained ambulatory pharmacists on smoking cessation rates in QatarSecondary: To assess the change in health-related quality of life in quitters vs. non-quittersSecondary: To explore the resource utilization of implementing the smoking cessation program as delivered by the ambulatory pharmacists in Qatar. This is a cost analysis of the overall cost of running the proposed patient-specific cessation program, including cost-effectiveness analyses.

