### Initial appointment and randomization

One to two days before his or her scheduled appointment, the study pharmacist contacts the enrolled participant to remind him or her about the appointment. At this initial appointment, which takes around 30 min, the study pharmacist first collects the participant’s sociodemographic characteristics, current medical problems and medications, smoking history (i.e., number of cigarettes per day, duration of smoking, previous quit attempts, smoking habits of other family members and the participant’s reasons for wanting to quit smoking) and vital signs (i.e., blood pressure and pulse). In addition, the pharmacist assesses the smoker’s level of nicotine dependence using the Fagerstrom Test for Nicotine Dependence and measures his or her baseline exhaled carbon monoxide (CO) level using the exhaled CO test. Furthermore, the pharmacist administers the smoking cessation quality-of-life (SCQOL) questionnaires. After baseline data collection, the smoker is randomly assigned to either the intervention group or the control group. Randomization is already anonymously preset by the study statistician for each study pharmacist. According to the participant number and the preset list, the participant will be randomized to the intervention or control group. A new appointment is set with the participants assigned to the intervention group. Participants assigned to the control group receive brief unstructured smoking cessation advice as outlined below. Participants in both groups do not pay for their participation.

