### Data analysis

The CONSORT guidelines will be followed when analyzing the study data. Demographics and other variables related to smoking and quality of life will be summarized using frequency distributions (for categorical variables) and means with standard deviations (for numeric variables) and will be compared between the two study arms using the chi-squared test (or alternatively the Fisher’s exact test for small cell counts) for categorical variables and the independent *t*-test (or alternatively the Wilcoxon rank sum test for non-normally distributed variables) for numerical variables.

The main outcome will be continuous abstinence at 12 months as self-reported and verified by the CO test. The percentages of participants achieving the main outcome will be computed and compared between the two groups using the chi-squared test. Moreover, the difference in the proportions of continuous abstinence at 12 months between the two study arms (with 95% confidence intervals) will be computed along with the number needed to treat. Multiple logistic regression will be used to obtain the odds ratio of the main outcome between the two study arms adjusting for any imbalances in demographics or other baseline smoking-related variables. Moreover, mixed effects logistic regression, with pharmacy-level random effect, will be considered to adjust for the possible pharmacy effect if it existed. The intent-to-treat principal will be used in the analysis whereby participants who will be lost to follow-up will be classified as smokers and included in the main analysis. This includes those who were removed from the study because they could not tolerate NRT side effects. A sensitivity analysis following that of Borelli, Hogan et al. will be done where the outcome has three possible categories: abstinence, no abstinence and dropout [48]. The suggested multinomial model will allow assessing factors affecting abstinence as well as factors affecting dropout. This will aid in understanding who might need more support during the intervention. Similar analyses for the primary outcome will be done at 3 and 6 months (but do not include verification of abstinence using CO tests).

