To assess the participants’ health-related quality of life, SCQOL (smoking cessation quality of life) ratings for each question will be translated into scores. A total health-related quality of life score and a domain-specific score will be calculated at baseline, 3 months, 6 months and 12 months for each participant in the intervention and control groups. The change in the total and domain-specific quality-of-life score from baseline will be calculated for each participant at 3, 6 and 12 months and analyzed using linear mixed models, which will include the quitting (quitters and non-quitters) factor and time factor (at 3, 6 and 12 months) and their interaction.

There is no interim analysis planned for this trial. Statistical analyses will be conducted using the Statistical Package of Social Sciences (IBM-SPSS®), version 21. In all analyses, the level of significance will be set at 5%.

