### Sample size calculation

For a priori sample size calculation, we assumed a 7-day point prevalence abstinence at 12 months of 3% for the control group and 15% for the intervention group based on the results of one of the previous studies that assessed the effect of a pharmacist-run smoking cessation program [12]. With a two-sided alpha of 5% and 90% power, a minimum sample size of 118 participants was estimated for each group. This sample size was not adjusted for the potential correlation between outcomes of patients within each clinic since this is not a clustered randomized clinical trial, but in this study patients within each clinic are randomized to the two intervention groups, and correlations, if they exist, will be very small; their effect on the power of the study is negligible [15]. The project has a total of 17 study pharmacists. Each study site is expected to enroll at least 30 participants (15 participants in the intervention group and 15 participants in the control group). The recruitment period is over 12 months (48 weeks). Recruiting at least 30 participants at each study site is considered feasible given that at least 100 patients visit each pharmacy per day. Assuming each study site will recruit 1 participant every week, the 30 needed participants will be recruited in 30 weeks (approximately 8 months). An extra 16 weeks of recruitment time is given to study pharmacists to account for workload, holidays and sickness.

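### The hypothesis that quitting improves quality of life is tested between self-selected quitters and non-quitters in a model that names no baseline covariate, so it is open to confounding of unknown size and direction

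*Protocol article*

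**What the plan says.** In the Protocol article, Study objectives states the hypothesis: "We also hypothesize that quitting smoking would lead to significant improvement in health-related quality of life". The matching secondary objective, and the corresponding entry under Outcome measures, set this up as change from baseline in quitters against non-quitters.

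Under Data analysis, change in the total and domain SCQOL scores at 3, 6 and 12 months is to be analysed with "linear mixed models, which will include the quitting (quitters and non-quitters) factor and time factor (at 3, 6 and 12 months) and their interaction". No baseline covariate is named.

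Initial appointment and randomization shows what is on file before allocation: "sociodemographic characteristics, current medical problems and medications, smoking history", and also "level of nicotine dependence using the Fagerstrom Test for Nicotine Dependence and measures his or her baseline exhaled carbon monoxide (CO) level". The smoking history includes cigarettes per day, duration, past quit attempts and smoking in the family.

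Covariate adjustment is stated for the abstinence outcome only: "Multiple logistic regression will be used to obtain the odds ratio of the main outcome between the two study arms adjusting for any imbalances".

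**The concern.** Quitting is an outcome of the trial, not an assigned treatment, so randomisation does not balance the two groups being compared. Smokers who manage to quit may differ at entry in dependence, consumption, illness or smoking at home. Any of these may also predict how SCQOL scores move over the year. If so, the coefficient for quit status mixes an effect of quitting with the difference in who quits.

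The protocol plans covariate adjustment for the randomised comparison, which needs it less, and names none for the non-randomised one. Followed as written, it would let a causal statement about quality of life rest on an unadjusted comparison of self-selected groups. Depending on the direction of the bias, a benefit could be overstated or a real one understated.

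**Working it through.** **The plan's own figure.** Inputs from Sample size calculation: "we assumed a 7-day point prevalence abstinence at 12 months of 3% for the control group and 15% for the intervention group"; "With a two-sided alpha of 5% and 90% power, a minimum sample size of 118 participants was estimated for each group". With the pooled-variance formula and no continuity correction:

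n = [1.960·√(2·0.09·0.91) + 1.282·√(0.03·0.97 + 0.15·0.85)]² / 0.12² = (0.793 + 0.507)² / 0.0144 ≈ 117.4, rounded up to 118.

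The stated 118 per group is reproduced. It is sized for abstinence; no figure is given for quality of life.

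**Size of the quitter contrast.** I apply the same abstinence rates to quit status, which is an assumption because Data analysis does not say which abstinence definition makes a quitter in this model.

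- Quitters: 118 × 0.03 + 118 × 0.15 = 3.5 + 17.7 = 21.2
- Non-quitters: 236 − 21.2 = 214.8
- SE of the difference in SD units: √(1/21.2 + 1/214.8) = 0.227

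**Illustration of the bias.** The documents give neither association needed here, so both are assumed over a range. Suppose there is no effect of quitting, one standard-normal baseline index L (dependence or ill health), a quit odds ratio per SD of L of 0.7 or 0.5 with arm rates held at 3% and 15%, and a correlation r between L and SCQOL change.

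The unadjusted bias is |r| × D, where D is the gap in mean L between non-quitters and quitters. D is 0.34 SD at odds ratio 0.7 and 0.63 SD at odds ratio 0.5. These values can be read off a large simulated population: at |r| = 0.2 the spurious differences were 0.068 and 0.126 SD, and 0.068/0.2 = 0.34 and 0.126/0.2 = 0.63.

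The rejection rate is approximately P(|Z + bias/0.227| > 1.96).

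| Quit OR per SD | Absolute r | Bias (SD) | Two-sided rejection |
|---|---|---|---|
| 0.7 | 0.1 | 0.03 | 5.3% |
| 0.7 | 0.2 | 0.07 | 6.0% |
| 0.7 | 0.3 | 0.10 | 7.3% |
| 0.5 | 0.1 | 0.06 | 5.9% |
| 0.5 | 0.2 | 0.13 | 8.6% |
| 0.5 | 0.3 | 0.19 | 13.2% |
| 1.0 | any | 0 | 5% |

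Simulated trials of this size agree within simulation error. A stronger assumption, |r| = 0.5 with odds ratio 0.5, gives 0.31 SD and 28%.

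**Direction.** If higher L goes with a worse course (r negative), the bias favours quitting. If higher L goes with more improvement (r positive), the same sizes apply with the sign reversed. With odds ratio 0.5 and r = 0.2 to 0.3, a false result in favour of quitting then has probability P(Z > 1.96 + 0.55) = 0.6% to P(Z > 1.96 + 0.83) = 0.3%, below the nominal 2.5%.

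**Effect of adjustment.** Adding L to the model returns rejection to about 5% to 6%. That follows from the set-up, which has a single confounder measured without error, and does not forecast how well adjustment would work in the trial.

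**The case against.** The strongest reply concerns direction. The outcome is change from baseline, so stable differences in level between quitters and non-quitters already drop out, and a confounder must predict the change itself. Healthier, less dependent smokers may start with higher scores and have less room to improve, in which case the bias runs against the hypothesis. This stands. A reader might infer that the quit effect is biased upwards and that the hypothesis would be wrongly confirmed; the documents do not support that, because they fix neither the sign nor the size.

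Magnitude is also a fair point. At odds ratio 0.7 the bias is at most 0.10 SD, less than half the standard error, and rejection stays near 5% to 7%. The illustration uses one time point and a fixed quit status, while the plan models three visits.

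Screening and eligibility criteria further narrow the contrast: entry is limited to smokers in the preparation stage, and several serious cardiac conditions and interfering psychiatric illness are excluded. That limits variation in motivation and severe illness, but leaves dependence, consumption and milder illness free to vary.

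Two further replies carry less weight. The objective and outcome entries are worded descriptively, but the hypothesis they serve is causal and nothing shown limits the conclusion to an association. An unseen analysis plan might add covariates, and the text does not say that the named terms are the only ones. Yet this document names the model terms itself and states adjustment only for abstinence, so an analysis plan that followed it would carry the problem forward. This lowers confidence without removing the point.

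**Conclusion.** The point holds in a limited form. The protocol pairs a causal hypothesis with a non-randomised contrast and names a model without the baseline variables it collects. The contrast is open to uncontrolled confounding of unknown size and direction; whether the result would in fact be biased cannot be established from the documents.

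Over the assumed range (odds ratio 0.5 to 0.7 per SD, |r| 0.1 to 0.3) the bias is about 0.03 to 0.19 SD either way, with two-sided rejection of about 5% to 13%. If the baseline variables do not predict quitting, there is no bias from them. This touches one secondary objective and leaves the randomised abstinence comparison intact. It is worth correcting because the correction is nearly free, not because a false claim has been shown to be likely.

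**What to change.** In the SCQOL mixed models, prespecify a short list of baseline covariates already collected, for example FTND score, cigarettes per day, age, sex and presence of current medical problems. Report the adjusted quitter versus non-quitter difference as the main result for this objective, with the unadjusted difference beside it. Reword the hypothesis and the planned conclusion so that quitting is associated with a change in quality of life, and state that adjustment removes measured confounding only; motivation, stress and social support, for instance, may remain.

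The cost is a change of wording and a few more model terms, which about 236 participants can support, and a slightly less favourable claim. No new data are needed. Trial status reports that recruitment is ongoing, so the change can still be made before the outcome data are complete.
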